### Intervention Fidelity and Training of Study Staff

Intervention fidelity is guided by recommendations from the National Institutes of Health Behavior Change Consortium [43], with attention to design, training, delivery, receipt, and enactment. Study staff at each site are involved in recruitment, retention, and data collection. Training addresses protection of human subjects, research compliance, study methods, data entry and management, roles and responsibilities, training on the C-SCAT intervention, and attention to the UCCG. All staff complete required human subjects and other relevant training at initiation of the project and throughout as appropriate.

To ensure that the intervention is delivered as intended within and across sites, we developed a standard operating procedure manual with core procedures for all sites and specific considerations within sites and ensured training for the study staff on procedures and interventions through review of the manual, didactic sessions, and demonstrations. To maintain consistency of training, study procedures based on the manual are regularly reviewed with the study staff. To mitigate bias by study staff during study visits for both arms, we have carefully scripted each study visit to support consistent delivery. The project coordinator monitors intervention delivery and receipt by routine random checking for any differences in study logs, completion of the C-SCAT, and completeness of measures. Retraining is instituted as needed. The research team holds twice monthly meetings (and ad hoc as needed) with study staff to discuss any issues with study procedures. To confirm intervention enactment, at the beginning of each intervention visit, study staff ask the participant what questions they have on how to complete the C-SCAT, and whether they want another practice session. These processes will ensure consistency of intervention delivery and integrity of data collection.

### Outcome Measures

#### Primary Outcome Measures

Self-efficacy is measured with the Patient-Reported Outcomes Measurement Information System Self-efficacy of Symptom Management Scale (PROMIS S-E), a domain-based 28-item scale. Items assess the person’s current level of confidence to manage or control symptoms, manage symptoms in different settings, and keep symptoms from interfering with work, sleep, relationships, or recreational activities [44]. Response options are on a 5-point Likert scale (1=*I am not confident at all* and 5=*I am very confident*). Scores are summed across items and can range from 28 to 140, and higher scores indicate greater self-efficacy. Cronbach α in our previous study with AYAs was 0.94 [45].

Symptom self-management is measured with the Symptom Self-management Behaviors Tool (SSMBT) [46]. The SSMBT contains 12 items with two subscales: manage symptoms (8 items) that address behaviors related to managing their symptoms and talk to health care provider (4 items) that address behaviors related to communicating with their HCP about their symptoms. Response options are on a 5-point Likert scale (0=*never* and 4=*always*). Scores are summed across all items. Higher scores indicate higher engagement in symptom self-management behaviors. The SSMBT was developed for AYAs with cancer and has evidence of being reliable and valid [46]. Reliability for the total scale was *α*= of .74. Construct validity was supported via principal component factor analysis and discriminant validity.

#### Secondary Outcome Measures

Symptom severity and distress in the past week are assessed using the MSAS [42]. Participants rate the severity on a 4-point Likert scale (1=*slightly* and 4=*very severe*) and the distress on a 5-point Likert scale (0=*none* and 4=*very much*). The adult version of the MSAS was used because it has 2 more symptoms (feeling bloated and problems with sexual interest or activity) than the MSAS 10‐18. In our previous study, AYAs indicated that these symptoms were relevant to them.

Two aspects of social function are assessed: quality of life related to social function and satisfaction with social function. Quality of life related to social function is assessed with the PROMIS SF (version 2.0) Ability to Participate in Social Roles and Activities. It contains 8 items, is scored on a 5-point Likert response scale (5=*never* and 1=*always*), and has strong evidence of reliability and validity in clinical populations, including individuals with cancer [47]. Satisfaction with social function is assessed with the PROMIS SF version 2.0 Satisfaction with Social Roles and Activities. It contains 8 items, is scored on a 5-point Likert response scale (1=*not at all* and 5=*very much*), has been validated in adults aged ≥18 years [48], and has been used in young adults with cerebral palsy [49].

#### Descriptive Measures

Self-reported demographic data are collected with the Biomedical Research Informatics Computing System, National Institute of Nursing Research [50] demographic form, including education, primary caregiver, employment, marital status, and household member count. Additional items assess household income, number of children, people living with the AYA, and living arrangement changes during treatment. Self-reported race and ethnicity are also being collected. Clinical and other descriptive variables are collected by study staff from the participant’s electronic health record and include age, sex, cancer diagnosis, time since diagnosis, chemotherapy protocol start date, treatment protocol, comorbid conditions, insurance type, and ZIP code.

#### Intervention Acceptability

Participants in the intervention group are asked to complete the C-SCAT Intervention Acceptability Survey. This 7-item survey assesses the acceptability of various aspects of the intervention, such as “How much effort did it take to do the CSCAT? and “How confident did you feel that you could complete the C-SCAT as instructed?”

### Data Collection

Data collection occurs at 3 time points (times 0, 1, and 2) at scheduled inpatient or outpatient visits (Figure 2). Baseline measures are collected at time 0, postintervention measures at time 1, and follow-up measures at time 2. Participants complete measures on a study-dedicated tablet computer using REDCap, or via a link to REDCap that is emailed to them. Study staff obtain clinical data from the electronic health record. The time 1 visit for the C-SCAT group is scheduled 2 weeks±7 days (to accommodate schedule changes) after completion of the intervention to allow time for the participant to have been at home (or outside the clinical setting) to self-manage their symptoms following chemotherapy. The time 1 visit for the UCCG group is scheduled 2 weeks±7 days (to accommodate schedule changes) after completion of the attention control visits. For both groups, the time 1 visit occurs during a scheduled inpatient or outpatient visit. Participants who are not scheduled for an inpatient or outpatient visit during the ±7-day window are contacted via telephone to complete the study measures and are sent a REDCap link via email. For both groups, the time 2 visit is scheduled 4 weeks±7 days from Time 1, and the same procedures for data collection as described earlier for time 1 are used.

### Safety

#### Data Safety Monitoring

This study carries less than minimal risk to participants. As this study is a multisite clinical trial and involves adolescents aged ≥15 years, we use a Safety Monitoring Committee to assess the safety of the study and monitor the data. The Safety Monitoring Committee consists of 2 members who have areas of expertise in AYAs with cancer and biostatistics. The Safety Monitoring Committee was established through the primary study site.

#### Monitoring Participant Safety

The research team uses a clearly defined protocol to monitor participant safety. Participant safety is monitored monthly and with each occurrence of a potential safety issue. The principal investigator, in collaboration with coinvestigators or site principal investigators, is responsible for monitoring the safety of participants at each site.

### Data Analysis Plan

#### Overview

This study is a 2-group (C-SCAT vs control), longitudinal randomized multicenter (5 sites), clinical trial with data collected at 3 time points (times 0, 1, and 2). Two primary variables are being evaluated for group differences in aim 1: symptom self-efficacy as measured by the PROMIS Self-Efficacy of Symptom Management Scale (PROMIS S-E) and self-management behaviors as measured by the SSMBT. The secondary outcomes in aim 2 are symptom severity, symptom distress, social function, and satisfaction with social function. The plan is to enroll 126 AYAs with cancer in active treatment from 5 sites. The study biostatistician who was not involved with data collection and will be blinded to group affiliation will conduct all analyses.

#### Sample Size and Power

A mixed effects linear model is planned to test for group differences across time for aims 1 and 2. The co-primary outcome variables from aim 1 are the PROMIS S-E and the SSMBT. From the outset, we planned to take a more conservative approach to the power analysis due in part to the limited number of SSMBT samples observed from only one site. Thus, for both primary variables, power was estimated using a 20% inflated variance estimate and a target power of 90% (as opposed to the usual 10% inflated variance and 80% power). A 20% inflated estimate of the residual SE was estimated as 12.73 for PROMIS S-E and 6.35 for SSMBT. Assuming the smallest clinically significant difference between the groups of 10 for PROMIS S-E and 4.8 for SSMBT, a Bonferroni adjusted alpha of .05/2=.025 and a power of 90%, PASS (Power Analysis & Sample Size, PASS 2022; NCSS, LLC [51]) software estimated the total sample size to be 77 for PROMIS S-E and 83 for SSMBT. However, the proposed model will have effects for time (0, 1, and 2), group (C-SCAT vs usual care), time-by-group interaction, site (1, 2, 3, 4, and 5), site-by-group interaction, and population (adolescent vs young adult). Accounting for the 16 degrees of freedom necessary to fit these model effects, the total sample size will be 83+16=99 who complete time 2. Allowing for an attrition as high as 20%, the final sample size will be 126 AYAs or approximately 25 per site. Recruitment in our preliminary multisite studies demonstrated that this sample size is feasible within the proposed period of the project.

Descriptive statistics will be computed for demographic and all outcome variables. All data will be examined graphically to determine the distributional properties. In cases of nonnormally distributed data, transformations may be used for analyses.

#### Aims

Aim 1 is to determine the effects of the C-SCAT versus usual care on the primary outcomes of self-efficacy for symptom management and symptom self-management behaviors immediately postintervention (time 1) and at follow-up 1 month later (time 2). Self-efficacy for symptom management and symptom self-management behaviors will be assessed at times 0, 1, and 2 and will be compared between the C-SCAT intervention group and the UCCG. We anticipate using a linear mixed effects model to test the effect of the C-SCAT versus usual care. The general form of the mixed linear model [52-54] is given by y=XB+ZU+ e, where y is the observed data vector (PROMIS S-E and SSMBT), X is a known design matrix, B is a vector of unknown fixed effects, Z is a known design matrix, U is a vector of unknown random effects, and e is a vector of unknown random errors. This model will include a random effect for participant (represented by ZU in the equation) and fixed effects for group (C-SCAT and UCCG), time (0, 1, and 2), group-by-time interaction, site (1, 2, 3, 4, and 5), group-by-site interaction, and population (adolescent and young adult; represented by XB in the equation). The model is flexible enough to accommodate the potential cofactors of race (eg, Black and White), ethnicity (eg, Hispanic and non-Hispanic), and gender (eg, male and female). The first step in testing aim 1 will be to test each of the primary variables (PROMIS S-E and SSMBT) using a contrast on the group-by-time interaction to specifically test for an immediate effect of C-SCAT versus the UCCG at time 1. A Bonferroni correction (*α*=.05/2=.025) is planned to adjust for testing each of the 2 primary variables. All other tests, for example, testing for a sustained effect at time 2, are considered supportive and will be testing with an *α* of .05. Modeling assumptions such as normality and homoscedasticity will be checked for each model. In the case of positively skewed data, a transformation (such as a log transformation) will be used to normalize the data. It is anticipated that all analyses will be performed using JMP (JMP 18, 2025 JMP 18; JMP Statistical Discovery LLC [55]) and SAS/STAT (Statistical Analysis Software Institute [56]) software, specifically PROC MIXED.

Aim 2 is to examine the effects of the C-SCAT versus usual care on secondary outcomes (symptom severity, symptom distress, quality of life related to social function, and satisfaction with social function) immediately postintervention (time 1) and at follow-up 1 month later (time 2). The mixed effects linear model presented in the aim 1 analysis plan is anticipated to be sufficient for the analysis of the secondary outcomes in aim 2. The secondary outcomes are considered supportive of the tests of an immediate effect (aim 1) and will be tested with an *α*= of .05.

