### Trial Design

This study uses a multisite 2-group RCT design to evaluate the effects of the C-SCAT for improving symptom self-management versus usual care in AYAs who are within the first 3 months of a cancer diagnosis and who are receiving cancer treatment. For this study, cancer treatment is defined as a prescribed infusion (eg, chemotherapy or immunotherapy). Data collection occurs at 3 time points (times 0, 1, and 2). Time 0 (baseline, followed by randomization) occurs at or near the enrollment visit. The C-SCAT intervention period is approximately 12 weeks, depending on the participant’s treatment schedule. Time 1 (postintervention) occurs approximately 2 weeks (±7 d) after completion of the intervention. Time 2 (follow-up) occurs approximately 4 weeks (±7 d) after time as seen in Figure 2.

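### As written, the random participant effect gives one correlation for all visit pairs, although times 0–1 are up to about 14 weeks apart and times 1–2 about 4, so the SE of a time 0-to-1 change contrast can be wrong in either direction

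*Protocol article*

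**What the plan says.** The Aims section of the protocol article introduces the analysis tentatively: "We anticipate using a linear mixed effects model to test the effect of the C-SCAT versus usual care". It gives the general mixed-model equation and then fills in its parts. For the random part: "This model will include a random effect for participant (represented by ZU in the equation". The fixed part holds group, time, group-by-time, site, group-by-site and population. The error term gets only this: "e is a vector of unknown random errors". No random slope and no residual covariance structure is named. The software is SAS/STAT, "specifically PROC MIXED", alongside JMP. Aim 2 reuses the same model.

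The primary test of each co-primary outcome, at a Bonferroni level of .025, is made by "using a contrast on the group-by-time interaction to specifically test for an immediate effect of C-SCAT versus the UCCG at time 1". On diagnostics: "Modeling assumptions such as normality and homoscedasticity will be checked for each model".

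On timing, Trial Design says "The C-SCAT intervention period is approximately 12 weeks", subject to the participant's treatment schedule, and "Time 1 (postintervention) occurs approximately 2 weeks (±7 d) after completion of the intervention". Data Collection puts time 2 four weeks (±7 days) after time 1. The description of the C-SCAT group has three intervention visits, with treatments typically 2 to 4 weeks apart.

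**The concern.** A random participant intercept with independent, constant-variance errors is compound symmetry: every visit has the same variance and every pair of visits the same correlation. The SE of a time 0-to-1 change then uses a residual variance averaged over all three visit pairs, including the close pair, times 1 and 2. If those two visits correlate more strongly than times 0 and 1, the average understates the variance of the change being tested. If time 2 is more variable than the other visits, or times 0 and 1 happen to be close, the average overstates it.

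At stake is whether each primary test has the declared level of .025. An SE that is too small raises the false-positive rate. One that is too large costs power. The two assumption checks that are named do not address within-participant correlation.

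**Working it through.** **Inputs from the article.** The nominal level is .025 per primary outcome (two-sided is assumed here, as the article does not say). About 99 participants complete time 2. Three cycles of 2 to 4 weeks take 6 to 12 weeks. Adding 2 weeks puts time 1 at about week 8 to 14, and time 2 follows 4 weeks later. The article gives no between-visit correlations and no per-visit SDs, so there is no figure of its own to reproduce, and all correlations and SD ratios below are assumptions.

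**Formula.** Write r01, r02, r12 for the three correlations. With complete data, the random-intercept residual variance estimates half the average variance of the three pairwise differences. With equal variances:

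- model variance ÷ true variance of the change contrast = (1 − mean r) / (1 − r01)
- SE ratio = square root of that
- true size = 2 × [1 − Φ(2.241 × SE ratio)]

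So the SE is too small exactly when r01 lies below the average of r02 and r12.

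**Correlation decay, equal variances**

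| r01 / r02 / r12 | mean r | variance ratio | SE ratio | true size |
|---|---|---|---|---|
| .50 / .50 / .50 | .500 | .50/.50 = 1.000 | 1.000 | 2.5% |
| .70 / .65 / .80 | .717 | .283/.30 = .944 | .972 | 2.9% |
| .50 / .45 / .75 | .567 | .433/.50 = .867 | .931 | 3.7% |
| .40 / .35 / .70 | .483 | .517/.60 = .861 | .928 | 3.8% |
| .30 / .25 / .70 | .417 | .583/.70 = .833 | .913 | 4.1% |

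**Effect of the time 0–1 gap.** Here the correlation is assumed to be .85 per 4 weeks, decaying exponentially, with time 2 four weeks after time 1:

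| time 1 at week | r01 / r02 / r12 | SE ratio | true size |
|---|---|---|---|
| 14 | .566 / .481 / .850 | .920 | 3.9% |
| 10 | .666 / .566 / .850 | .957 | 3.2% |
| 8 | .722 / .614 / .850 | .988 | 2.7% |
| 6 | .784 / .666 / .850 | 1.039 | 2.0% |

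Week 6 lies below the 8-to-14 range. It would need two-week cycles with the first intervention visit on the baseline day (2 × 2 + 2 = 6).

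**Unequal variances.** Take SDs of 1, 1 and 1.3, and correlations of .50/.45/.70. The variances of the pairwise differences are:

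- times 0–1: 1 + 1 − 2(.50) = 1.00
- times 0–2: 1 + 1.69 − 2(.45)(1.3) = 1.52
- times 1–2: 1 + 1.69 − 2(.70)(1.3) = 0.87

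Their average is 3.39/3 = 1.13, against a true 1.00. The SE ratio is √1.13 = 1.063 and the true size 1.7%.

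**Simulation check** (about 99 participants, complete data). For the .50/.45/.75, .40/.35/.70 and .30/.25/.70 cases, the compound-symmetry test had a size of about 3.6–4.1%. Estimating the variance of the change directly, which is essentially what an unstructured covariance does with complete data, gave 2.4–2.6% in every case, including equal correlations and the larger time 2 SD.

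**Alternative contrast.** If the primary test is the plain group difference at time 1, compound symmetry with equal variances gave a size of 2.3–2.4%, so there is no inflation.

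**The case against.** The strongest objection is that the article does not fix compound symmetry. It never says that the errors are independent, it presents a general form and an anticipated model, and PROC MIXED accepts a structured residual. A condensed article commonly leaves that detail to an analysis plan, which is not shown here. The list of assumption checks is also given as examples, so a check of the correlation structure is not excluded.

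Much of this stands. A reader might infer that the plan forces equal correlations, and the text does not support that: it holds only if nothing is added to the model. But the article is not merely silent. It names a participant random effect as the within-participant term, and coding that as written, with no further structure, gives compound symmetry. A fully unstructured residual would have to replace that term, because the two cannot be separately identified.

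The second objection concerns direction. A reader might infer that the SE is probably too small and the .025 level therefore breached. The documents do not support that either. They give no correlations or visit-specific variances, 14 weeks is the upper end of the gap, the effect nearly vanishes at 8 weeks, and it reverses with a larger time 2 SD or a very short gap. It also depends on reading the contrast as a change from baseline. That is the natural reading of a contrast on the group-by-time interaction, but the sentence could also mean the group difference at time 1. This objection stands in full, and the point is therefore limited to an error in either direction.

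**Conclusion.** The point holds in a conditional form. If the stated term is fitted without a residual structure, and the primary contrast is the change from time 0 to time 1, the SE is tied to an equal-variance, equal-correlation pattern that the uneven schedule gives little reason to expect. Under assumed decay with equal variances, the SE is about 1–9% too small and the true size about 2.7–4.1% at nominal 2.5%. In the reversing cases it is 4–6% too large, with a size of about 1.7–2.0%. These figures rest on assumed correlations and SDs, complete data and a two-sided test.

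The effect is modest, and it is not shown that either primary test will be anti-conservative. The change is still worth making: the unstructured alternative held the level in every case examined and loses almost nothing if the correlations turn out equal.

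**What to change.** In PROC MIXED, replace the random participant effect with an unstructured 3×3 within-participant covariance (REPEATED time / SUBJECT=participant TYPE=UN) and Kenward-Roger degrees of freedom, for all Aim 1 and Aim 2 models. Prespecify a fallback if it does not converge: compound symmetry with robust SEs. State in the same sentence whether the primary contrast is the group difference in change from time 0 to time 1 or the group difference at time 1.

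The cost is one line of code and four more covariance parameters (six instead of two), which is small with about 99 completers and three visits. Recruitment was still open when the article was written, with closure expected in Fall 2026, so the change can be made before the data are analyzed.

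### The primary Aim 1 model leaves the arms' baseline means free; a baseline-adjusted time-1 test would gain precision at no cost, and restated power should name its contrast, SD and correlation

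*Protocol article*

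**What the plan says.** Under Data Analysis Plan, Aims, the Aim 1 model has fixed effects for group, time (levels 0, 1 and 2), group-by-time, site, group-by-site and population. Participant is the only random effect. The primary test for each outcome is made "using a contrast on the group-by-time interaction to specifically test for an immediate effect of C-SCAT versus the UCCG at time 1", at alpha .025. The baseline score is not among the covariates, and nothing sets the arms' time-0 means equal. Trial Design places the baseline measurement before randomisation.

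Sample Size and Power says: "A 20% inflated estimate of the residual SE was estimated as 12.73 for PROMIS S-E and 6.35 for SSMBT". The other inputs are a "smallest clinically significant difference between the groups of 10 for PROMIS S-E and 4.8 for SSMBT", and "a Bonferroni adjusted alpha of .05/2=.025 and a power of 90" percent. PASS "estimated the total sample size to be 77 for PROMIS S-E and 83 for SSMBT", and after an addition for model degrees of freedom "the total sample size will be 83+16=99 who complete time 2". No correlation between visits is given, the PASS procedure is not named, and the model behind the residual SE is not identified.

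**The concern.** Time 0 precedes randomisation, so the arms have the same expected baseline by design. A model with an unconstrained group-by-time term ignores this and estimates a separate baseline mean in each arm. If the time-1 contrast is the difference in change from time 0, it carries the full sampling noise of both baseline means. If it is the plain group difference at time 1, baseline contributes nothing. Either way, data already collected could sharpen the primary estimate and do not.

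This also affects how the power statement can be read. The precision of a change contrast depends on the correlation between time 0 and time 1, which are separated by an intervention period of about 12 weeks and roughly 2 further weeks. Without a stated contrast, SD type and correlation, a reader cannot tell what the 90% refers to. Precision matters here: Results puts enrolment at about 73% of the quarterly benchmark, and Limitations names recruitment as the main difficulty.

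**Working it through.** **Inputs** (Sample Size and Power): differences d = 10 and 4.8; s = 12.73 and 6.35; alpha .025 per outcome; 99 completers. Assumptions: two-sided tests, 1:1 allocation, equal variance at each visit, and one common correlation rho between visits (as the random participant effect implies). The article gives no rho, so a range is shown. Pairs are PROMIS S-E / SSMBT.

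**1. The plan's own figure.** A plain two-group formula gives N = 4(s/d)²(2.241+1.282)² = 80.5 / 86.9, or 82 / 88 with equal arms. The noncentral t gives 84 / 90. One-sided .025 gives 70–71 / 74–76. None returns 77 / 83. Multiplying the variance by about 0.92 in the t calculation does return 77 / 83. That factor would arise from baseline adjustment at rho of about 0.28 (1-0.28² = 0.92) or from a change contrast at rho of about 0.54 (2×0.46 = 0.92). The match does not show that either was used.

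**2. Variance factors.** Write the variance of the estimated effect as 4s²f/N, with s the total SD at one visit:
- change from time 0: f = 2(1-rho)
- raw time-1 difference: f = 1
- baseline-adjusted or constrained baseline: f = 1-rho²

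The ratio of adjusted to change is (1-rho²)/[2(1-rho)] = (1+rho)/2. A generalised least squares check on the three-visit model gave:

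| rho | change | raw time 1 | constrained baseline | constrained / change |
|---|---|---|---|---|
| 0.3 | 1.40 | 1.00 | 0.91 | 0.65 |
| 0.5 | 1.00 | 1.00 | 0.75 | 0.75 |
| 0.7 | 0.60 | 1.00 | 0.51 | 0.85 |

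For any rho strictly between 0 and 1, the adjusted factor is below both alternatives.

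**3. Power at 99 completers, if 12.73 and 6.35 are total SDs.** Noncentral t with noncentrality d/[s√(4f/99)] and 83 df (99 less the plan's 16). Example, PROMIS S-E at rho 0.3: the change contrast has SE 12.73×√(5.6/99) = 3.03 and noncentrality 3.30; the adjusted contrast has SE 12.73×√(3.64/99) = 2.44 and noncentrality 4.10.

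| rho | change | raw time 1 | adjusted |
|---|---|---|---|
| 0.2 | 79% / 75% | 95% / 93% | 95% / 94% |
| 0.3 | 84% / 81% | 95% / 93% | 96% / 95% |
| 0.4 | 90% / 87% | 95% / 93% | 97% / 96% |
| 0.5 | 95% / 93% | 95% / 93% | 99% / 98% |

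On the change reading, 90% needs rho of about 0.40 / 0.45.

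**4. If they are within-person residual SDs of the mixed model.** Then s² = 12.73²/(1-rho), and likewise for 6.35. The change contrast has variance factor 2 relative to 12.73², so power at 99 is 68% / 65% whatever rho is, and 90% would need 164 / 177 completers. The adjusted factor is (1-rho²)/(1-rho) = 1+rho, which gives 87% / 84% at rho 0.3 and 82% / 78% at rho 0.5. Adjustment still gains, but does not reach 90% at those values.

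**5. If they are already change-score or baseline-adjusted SDs,** the printed SD may match the planned or the adjusted contrast, and there may be no mismatch.

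**The case against.** The strongest reply is that nothing is broken. With randomised arms, a mixed model with baseline as a response and free group means is valid and unbiased; constraining or adjusting for baseline adds precision and corrects no error. That stands, and it sets the weight of this point.

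A reader might infer that the trial was sized with a simple two-group formula that ignored correlation. The article does not say so, and that formula does not reproduce 77 and 83.

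A reader might also infer that 90% power is missed. That is not shown. The words about an effect at time 1 also fit a raw time-1 difference, where power at 99 is 95% / 93% on the total-SD reading. On the change reading the required correlation is only moderate. Two margins help further. The 99 are completers of time 2, while the primary test is at time 1: if half of the 20% attrition fell after time 1 (an assumption; 126-12.6, about 113), change-contrast power at rho 0.3 would be about 89% / 87%. The SD was also deliberately inflated: dividing the variance by 1.2 gives about 91% / 88% at 99 and rho 0.3. The 68% / 65% figures rest wholly on the within-person reading.

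It is tempting to add that site, the stratification factor, does not adjust the primary test because time-constant terms drop out. That holds only for the change contrast with complete data. Nor does adjustment make power independent of rho; its variance is still s²(1-rho²).

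Finally, this is a condensed article. Contrast coefficients, the PASS module and the assumed correlation may be in the full protocol or analysis plan, so their absence is not itself a fault. The listed model terms are stated, however, and they do not use baseline for adjustment.

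**Conclusion.** The point holds as an inexpensive improvement. As written, the primary Aim 1 model leaves randomised baseline means free and forgoes precision under either reading of the contrast: the adjusted variance is (1+rho)/2 of the change contrast (35% lower at rho 0.3, 25% at 0.5, 15% at 0.7), or 1-rho² of the raw time-1 difference (9%, 25% and 49% lower). These sizes assume equal variances, a common correlation and complete data.

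Whether the stated 90% applies to the planned test is undetermined. It depends on which contrast is meant, what 12.73 and 6.35 measure, and rho. A shortfall is conditional on those readings and is not demonstrated. The conclusion about precision does not depend on them.

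**What to change.** Make the primary time-1 test baseline-adjusted, in one of two ways: a constrained longitudinal model with a common time-0 mean and a group effect only at times 1 and 2; or times 1 and 2 as outcomes with the baseline score as covariate. Keep site as a stratification covariate. Both are compatible with the plan's inclusion of participants with any post-intervention data.

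When restating power, say which contrast it is for, whether 12.73 and 6.35 are total, within-person, or change-score or adjusted SDs, and what correlation is assumed. Show results over a range of rho.

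The cost is revised model wording and a restated power sentence, with no new data or participants. Recruitment is expected to run to Fall 2026, so the change can be made before analysis. Restated power could look less favourable if the SDs turn out to be within-person residuals.
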